13.2 Data processing

Questionnaires will be completed during the active and passive surveillance conducted inside the compounds and the dispensaries.

Supervisors will check the questionnaires before they are passed to the computer desk. Supervisors will check for validity, compatibility and completeness of the returned questionnaires. Hence errors will be rapidly detected and corrected. on a daily basis, supervisors will finally go back to a random selection of compounds to verify the exactitude of data transmitted weekly by field workers.

Figure 2 shows how errors will be looked for carefully and managed before any data entry. After validation of data, transaction files will be used to update the database of the study with regards to integrity rules.

13.3 Measurements of study end-points and statistical analysis

In this study, sample size calculations are particularly done for the drug resistance end-point based on the 2002 study. Knowing that in the comparator group (AS1 + SP) the prevalence of genes with mutations markers of SP resistance increased from around 50% to 90%, the level of increase in the AS3 + SP could be looked at, with the assumption that it won’t be more than 50% to 70%.

The *dhfs*, *dhfr* and *pfcrt* genes from *Plasmodium falciparum* isolates taken on pre and post sIPT filter paper blood samples during the two cross sectional will be analysed by PCR-RFLP. Individual data will be tabulated according to the drugs regimen allocation.

The second end-point is an estimate of the effect of sIPT using the four regimens on the occurrence of the first or only clinical episode of malaria. The primary result is unadjusted protective efficacy, defined as (1-rate ratio). *Kaplan Meier Method* will be used to plot time-to-event analyses for first malaria attack after intervention, and *Log-rank* test to assess potential differences in the analyses.

Figure 2: Framework summarising the data management tasks

Back to the field

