**Follow-up:**

- From July 2004 to January 2005, participants will be visited at least once a week by 10 field workers
- Mothers or guardians will be asked about any episode of illness during the past seven days
- Children who have fever or any other symptoms potentially related to malaria will be follow up for at least the three following days
- Clinical attacks of malaria will be documented and treated without charge in Niakhar’s health centres by three qualified nurses
- *dhfr*, *dhps* and *pfcrt* mutations will be monitored in parasites obtained during two cross-sectional survey before and after the interventions
- This study will identify the best suitable combination for sIPT taking into account the risk of selection of drug resistant parasites

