2.2. Exclusion criteria

Reasons for exclusion will include any of the following:

Any conditions causing an inability to take or retain oral medication.

Any chronic illnesses or severe conditions such as tuberculosis, epilepsy, obvious mental retardation or failure to thrive.

Severe congenital diseases such as heart malformations

Intake of an anti-malarial other than chloroquine within the previous two weeks

Known allergy to any of the antimalarial drugs used in the trial.

1. Study design

We will use an open label randomised trial comparing the following regimens:

- Artesunate one day plus SP

- Artesunate given for three days plus SP

- Artesunate plus Amodiaquine both given for three days

- Lapdap for three days

One of these combinations will be randomly allocated to all participants and given three times in early September, early October and early November 2004.

1. Sample size calculations

The trial is powered as an ‘equivalence’ or ‘negative’ trial, with the outcome being the cumulative incidence of malaria, ie the proportion of children having at least one episode of malaria during the course of the study. AS3+SP is the comparator and is expected to have cumulative incidence of 20%, and we aim to show that this is no more than 30% in the other three arms. To allow for three comparisons — AS3+SP compared with each of the other three arms — we set the significance level to 5/3% (≈0.0167%), one-sided. With 80% power, we need 336 children per arm (Jones, Jarvis et al. 1996). We expect no more than 20% to be lost to follow-up, which raises this to 420 per arm, or 1680 in total.

For the secondary drug resistance endpoint, this implies 336×0.2=67 cases on AS3+SP. To be conservative, we assume the same number on the other arms (if they turn out to be less effective than AS3+SP, this will only increase the power for this secondary endpoint). Among these cases, based on our previous study, we expect the prevalence of *dhfr* mutations at codons 108, 59 and 51 to be 90% in the AS1+SP arm. The 67 cases per arm then give us 77% power to detect a difference of 20% (ie 70% prevalence) in the other arms, with a significance level of 5% (two-sided, (Fleiss 1981)).

1. Enrolment procedure and follow-up

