Participants will be surveyed during a period of four months, September to December, with regular home visits. Morbidity screening will be carried out weekly since less frequent surveillance has been shown to underestimate the number of cases substantially. All visits will be documented using a standard form (*appendix 3*). Two days treatment with Coartem®  will be given to cases of clinical malaria defined as children who are slide positive and who have a history of fever and or vomiting within the past twenty-four hours. (Rogier, Ly et al. 1999).

A consultation ticket (appendix 7) will also be handed to the child’s parent for free consultation at the nearest health centre where physical and parasitological examinations are immediately done. Children who have been treated for malaria will be revisited at least once a day until day 3 in order to see if the treatment is effective and the child has recovered well. If parasites are still present at day 3 treatment will be pursued using Quinine after confirmation that the previous treatment had been well taken and not vomited.

For the 28 days following any confirmed malaria attack, a child will not be considered at risk for determination of malaria incidence rates.

Because follow-up will be based on passive surveillance, it is intended to organize two cross sectional surveys (September and December). Asexual forms of parasites, gametocytes and packed-cells volume will be measured for every child.

An experienced supervisor employed by the IRD will control the performance of the field-workers by randomly re-visiting in the afternoon participants seen in the morning.

Treatment will be provided for free at the three main health centres in the study area.

1. Assessment of resistances to antimalarials

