# 17. Timing

# Actually the preparatory phase will begin in June 2004 at the latest with the informed consent operations. Five months data collections are planed (interventions and malaria morbidity follow-up), starting from September 1st, 2004.

18. Administrative considerations

The IRD Niakhar Project (Unité de Service Niakhar) will be responsible for the administrative aspects of the study . Particular attention will be given to avoidance of any interference with other malaria studies being conducted in Niakhar. After finalisation of the protocol, no changes will be permitted without the agreement of Research Advisory Panel as well as the Niakhar Project. Any change will be formally endorsed, and attached to the original protocol.

The project has already be presented to all the senior staff of the National Malaria Programme.

19. Budget

Details of the budget are given on appendix in the budget template.

19. 1. Personnel

An experienced team is needed for this demanding study. All payments have been worked out in accordance with Senegalese salary scales.

 Assistance of a computer engineer is fundamental. He will help with programming and, supervision of data entry activities. In close collaboration with the main investigator, he will be asked to produce monthly cross tabulations, which summarise the progress of work.

 An assistant field physician, newly graduated from the University of Dakar will help the principal investigator to ensure medical supervision 24 hours a day and 7 days a week throughout the study.

Three qualified nurses will strengthen the medical staff in existing health centres, as the trial will markedly increase the work pressures in these structures. The project activities must be complementary to health centre’s routine activities.

In order to achieve good follow-up of study children 8 field workers and 2 field-supervisors are needed. This number has been carefully determined according to the average number of compounds that a field worker visits in a day.

A qualified, experienced logistician will have under his responsibility all field materials

 At least two drivers are needed to facilitate communication within the team. They will also ensure transportation of staff from village to village as well as between Dakar and the field.

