**REFERENCES**

1. 1 Every child treated after confirmed malaria will lose 28 days of follow-up

   2 Kaplan Meier Method will be used to plot survival curves, and Logrank test to assess potential differences in the analysis [↑](#footnote-ref-2)
2. 2 [↑](#footnote-ref-3)
3. 1 An Ethno linguist consultant will translate in the information in Serer and Wolof [↑](#footnote-ref-4)
4. 1 Severity: 1=Mild, 2=Moderate, 3=Severe [↑](#footnote-ref-5)

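### The trial is sized to show a limit on cumulative malaria incidence (no more than 30% against 20%), but the stated primary clinical analysis is a rate ratio and a test for differences, which do not test that limit

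*Protocol*

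**What the plan says.** **Sizing (Protocol, Sample size calculations).** "The trial is powered as an ‘equivalence’ or ‘negative’ trial". The outcome is "the proportion of children having at least one episode of malaria during the course of the study". AS3+SP is the comparator, expected at 20%, and for this outcome "we aim to show that this is no more than 30% in the other three arms". The level is 5/3% one-sided, to allow for three comparisons with AS3+SP. Power is 80%, with 336 children per arm, or 420 after 20% loss to follow-up.

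**Hypothesis (section V).** The other regimens are expected to be as effective as SP with one dose of artesunate (AS1+SP). That is a different reference arm from the one used for sizing.

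**Analysis (section 13.3).** For the first or only clinical episode: "The primary result is unadjusted protective efficacy, defined as (1-rate ratio"). Kaplan-Meier plots and a log-rank test for potential differences accompany it. No reference arm is named for the rate ratio. The only comparator named in that section is AS1+SP, and it is named for the resistance outcome.

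**Follow-up.** Three statements are given:
- Study outline: "From July 2004 to January 2005, participants will be visited at least once a week by 10 field workers".
- Patient assessment section: "Participants will be surveyed during a period of four months, September to December, with regular home visits".
- Section 17, Timing: "Five months data collections are planed (interventions and malaria morbidity follow-up), starting from September 1st, 2004".

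**The concern.** The two sections differ in two ways. The first is scale: sizing uses an absolute difference in the proportion affected, and the analysis uses a ratio of rates. The second is the null hypothesis: sizing sets out to reject an excess of 10 points or more, while the log-rank test sets out to reject no difference at all.

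A test of no difference does not control the error that the sizing was meant to control, which is accepting a regimen that is materially worse. Failing to find a difference becomes easier as data become sparser, whereas showing that a limit is respected becomes harder. Since the hypothesis is one of equal effectiveness, the reported analysis should be able to support or refuse that claim at the planned error rate. As stated, it cannot.

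**Working it through.** **1. The plan's own sample size.** Inputs from the sample size section: true risk 20% in both arms, margin 30% − 20% = 10 points, power 80%, level 5/3%.

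n = [p₁(1−p₁) + p₂(1−p₂)] × (z₁₋α + z₀.₈)² / margin², where the bracket is 0.16 + 0.16 = 0.32.

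- One-sided 1.67%, as worded: 0.32 × (2.128 + 0.842)² / 0.01 ≈ 282, so 283.
- 5/3% split over two sides (one-sided 0.833%): 0.32 × (2.394 + 0.842)² / 0.01 = 335.01, so 336. This matches.
- Loss to follow-up: 336 / 0.8 = 420, and 4 × 420 = 1680. This matches.

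So 336 follows from a margin calculation on a risk difference, and it is somewhat larger than the one-sided wording needs. The printed approximation of 5/3% as 0.0167% is a slip for 0.0167 as a proportion.

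**2. Power if the analysis follows the sizing.** SE = √(0.32/336) = 0.0309. Power at one-sided 1.67% = Φ(0.10/0.0309 − 2.128) = Φ(1.11) = 86.7%. At one-sided 0.833% it is 80.1%.

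**3. What the log-rank test does at the limit.** Assume proportional hazards, 30% against 20%, and 336 evaluable children per arm.

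- Hazard ratio: ln(0.70)/ln(0.80) = 1.60.
- Expected events: 336 × (0.20 + 0.30) = 168.
- Expected z: ln(1.60) × √(168/4) ≈ 3.04.
- Probability of a non-significant result: 1 − Φ(3.04 − z₁₋α/₂).

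| Two-sided level | Formula | 20,000 simulated trials |
|---|---|---|
| 5% | 14.0% | 14.9% |
| 5/3% | 25.9% | 26.7% |

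Against the planned 1.67%, this is about 8 times (14.0/1.67) to 16 times (26.7/1.67) as high. It applies only if a non-significant result is taken as equivalence.

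**4. A single result on which the two approaches part.** Take 67/336 (19.9%) on AS3+SP and 84/336 (25.0%) on another arm. The log-rank p is about 0.11, so no difference is found. The risk difference is 5.06 points with SE 3.21 points, and its one-sided 1.67% upper limit is 5.06 + 2.128 × 3.21 = 11.9 points. The 10-point limit is not met.

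**5. The ratio scale does not carry the margin by itself.** A hazard ratio of 1.60 corresponds to 5.5 points at a reference risk of 10%, 10.0 points at 20% and 13.5 points at 30%. A ratio margin would have to be stated, and the protocol states none.

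**The case against.** Much can fairly be said for the protocol.

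- **No rule says that a non-significant test means equivalence.** A reader might infer that the trial would declare the regimens equally effective on that basis. The documents do not support this: section 13.3 says only that potential differences will be assessed. The error rates in step 3 are therefore conditional.
- **The margin is implied.** The sample size section gives an expected 20% and a ceiling of 30%. It does not say what applies if the comparator differs from 20%. Ten points is the natural reading and is consistent with 336, but it remains a reading.
- **A rate ratio could serve.** A confidence interval for it, read against about 1.60, would test a limit. The interval method and the analysis sets may be left to a statistical analysis plan that is not shown, and they are not counted here.
- **Protective efficacy is not meaningless.** A reader might say so because all four arms are active. The protocol defines it as one minus a rate ratio, which can be computed against any reference. What is missing is the named reference arm, and the label can mislead.
- **The follow-up windows conflict less than they seem to.** July and August precede the first dose in early September, and the endpoint is the first attack after intervention, so those months add no events. The real conflict is whether follow-up ends in December or in January.
- **The footnote is weak support.** "Kaplan Meier Method will be used to plot survival curves, and Logrank test to assess potential differences in the analysis" is attached to a list of monthly database outputs and is not clearly a rule for the final analysis.

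The central point remains after all of this. The protocol does not leave the analysis open. It names a primary result and a test, and neither matches the question it was sized for. A later analysis plan would have to override section 13.3, not merely add detail to it.

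**Conclusion.** The concern holds as a mismatch between the sample size section and section 13.3. The trial is sized to show that cumulative incidence stays within a limit (30% against 20%, one-sided 5/3%), and the stated clinical analysis does not test that limit. It needs correction before analysis.

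The possible cost is acceptance of a regimen truly at the limit in about 14-15% of trials (two-sided 5%) or 26-27% (two-sided 5/3%), against 1.67% planned. This rests on 336 evaluable children per arm, proportional hazards, true risks of 20% and 30%, and a non-significant log-rank test being read as equivalence, which the protocol does not state.

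A reader might also conclude that the trial is too small. It is not: 336 per arm is enough for the margin comparison.

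**What to change.** **Section 13.3.** Make the primary clinical analysis the difference in cumulative incidence (proportion with at least one episode, by Kaplan-Meier) between each other arm and AS3+SP, from first dose to one fixed date. Report a one-sided 1.67% upper confidence limit (two-sided 96.67% interval), and claim non-inferiority only if that limit is below 10 points.

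**Supportive analyses.** Keep the rate ratio, with AS3+SP named as reference and labelled a relative rate, noting that about 1.60 corresponds to 30% against 20%. Keep the log-rank test.

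**Reconcile:**
- the reference arm, between the Hypothesis (SP plus one dose of artesunate) and the sample size section (AS3+SP);
- the end of follow-up, between the patient assessment section (December) and the Study outline and section 17 (January).

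**Cost.** Rewording only. No extra children or data are needed.

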**Daily Codification &**

**Data entry**

**Weekly** checking of transaction files

**Weekly** Updating of the trial database

**Main trial database**

The database will be used to extract analysis files and to produce on a monthly basis statistical information such as:

- Basic demographic analysis of study population followed during the month (age distribution, sex ratio, geographic distribution etc…)
- Number of those followed up, lost to follow-up, died, refused and withdrawn
- Number of samples before and after the interventions
- Number of children who have been completely followed during the month
- Number of child-days a risk[[1]](#footnote-2)1
- Number of first fever, or first clinical malaria attacks
- Total number of fevers
- Total number of clinical malaria attacks
- Proportion of children free from malaria since the start of the trial[[2]](#footnote-3)2
- Proportion of children free from malaria since the last intervention
- Proportion of urine tests positive for chloroquine metabolites
- Proportion of serious adverse events after drug administration

# 14. Acceptability and safety

Tolerance and safety of the intervention will be based on analyses of observational and clinical information collected after each administration of a sIPT.

# 15. Ethical considerations

The conclusions of this study could influence malaria control policies in Senegal and in other parts of Africa. Parents and guardians will profit from the intensive surveillance activities during the study period. In addition, all malaria cases will be treated in health centres according to national policy. Thus, this study will not interfere or limit access of study participants to the national malaria prevention programme provided by the health services.

Three of the drug combinations to be used in the study, SP + one dose of artesunate, SP + three doses of artesunate and amodiaquine + artesunate have been used extensively to treat or prevent malaria in young children in Africa and their safety profiles are well known. There is less safety data for Lapdap but this drug is now licensed for the treatment of malaria in Europe and in many countries in Africa.

Informed and written consent will be obtained from parents or guardians. The study will explain the need to find an alternative to SP for seasonal IPT since this is important for future protection of their children.

Ethical approvals of the study will be sough from both:

- the Ethics review board of Research for Development Institute in France,
- the Senegalese Ethics Committee
- and the Ethics committee of the London School of Hygiene and Tropical Medicine.

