In that study, entomological data showed transmission rates of ten infective bites per person per year, mainly acquired during the rainy season. Most severe cases of malaria are observed in November, particularly among children less than five years old. The latest assessments of resistance for chloroquine, amodiaquine and SP have shown respectively 44%, 16% and 7% of resistant parasites (Sokhna, Molez et al.). Surprisingly, chloroquine is still used as first-line treatment in most government facilities despite official instructions of using SP plus amodiaquine as first line. In this area, malaria mortality occurs mainly in children under 5 years of age. From 1984 to 1992, it fluctuated between 2.3 and 7.4 deaths per thousand per year with an average of 4.2 per thousand. After the emergence of chloroquine resistance, it increased to 16 per thousand per year, representing the cause of one out of four deaths in the one to four years old age group (Trape et al. 1998).

1.4. Heath cares systems in Niakhar: The site has three health centres, each of them headed by a qualified nurse. Consultations are provided daily from Monday to Friday. Pre-natal and EPI activities are normally run according to national policies. These health structures receive the assistance of an IRD physician at least one day a week.

1. Inclusion and Exclusion criteria

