The first step will be to hold by June 2004 several community-meeting with all the partners involved in the trial including the villagers. Then, eligible children will be included if they meet the inclusion criteria and if their parents or guardians provide informed consent. The explanation provided to parents will be given in local languages, emphasising the potential public health impact for malaria control of the study (*appendix 1*). When approval is obtained after a medical examination, a study number will be allocated immediately (*appendix 2*). In addition, an ID card will be given to all participants to facilitate identification at every contact, at home or in the health centres. At the time of each drug administration, a clinical examination and an interview of parents will be performed. Children will pass through four teams respectively for identification, clinical examination, blood sampling and anti malarial drug administrations. Those who are febrile at a time of intervention will be tested for malaria and given two days treatment with Coartem® . Haemoglobin levels and drugs resistance markers will be assessed during two cross-sectional surveys conducted at the time of the first drug administration (September 04), and one month after the third and last drug administration (December 04).

1. Randomisation and drug distribution

Individual randomisation is proposed and will be done approximately three weeks before the first sIPT administration planned for early September 2004. Children will be given active drugs according to their allocation group. The investigators who do the randomisation will also separate the regimens into jars, and make a note of the code. They will therefore not be blind, but all field staff and lab staff involved directly in making observation on study subjects or their samples will be blinded to study group.

Individual notice will be given to all participants approximately one week before any intervention. Drugs will be given at the health centres.. For young children, tablets will be crushed, mixed with water and administered. All participants will be under observation for 15 minutes after drugs are taken. In case of vomiting, the drug will be re-administrated.

1. Patient assessment procedures & clinical management

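### The protocol gives two different rescue treatments for malaria cases, and one of them would put drugs under study into the control arms of the resistance comparison

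*Protocol*

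**What the plan says.** Four places in the protocol bear on how a study child with malaria is treated.

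- Section 5 (Enrolment procedure and follow-up), on the dosing rounds: "Those who are febrile at a time of intervention will be tested for malaria and given two days treatment with Coartem".
- Section 7 (Patient assessment procedures & clinical management), on surveillance between rounds: "Two days treatment with Coartem" is the treatment, and it "will be given to cases of clinical malaria defined as children who are slide positive" with recent fever or vomiting. Quinine follows if parasites persist at day 3.
- Section 15 (Ethical considerations): "all malaria cases will be treated in health centres according to national policy".
- Section 1.3 (Malaria transmission and mortality in Niakhar) describes practice and policy: "chloroquine is still used as first-line treatment in most government facilities", "despite official instructions of using SP plus amodiaquine as first line".

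Section 8 (Assessment of resistances to antimalarials) sets the resistance comparison. The artesunate-amodiaquine arm is the control for dhfr and dhps mutations. The SP and Lapdap arms are the controls for pfcrt mutations. Section 5 places the two marker surveys at the first round in September and one month after the last round, in December.

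**The concern.** A nurse at one of the three health centres cannot tell from the protocol which drug a study case receives. Sections 5 and 7 name one drug. Section 15 points to a policy whose only stated content is a different combination.

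The choice matters for more than tidy wording, because that combination is made of two drugs whose resistance markers are being compared. Resistance is one of the two major endpoints in section V. A control arm is useful for dhfr/dhps only if its children are not given SP, and for pfcrt only if they are not given amodiaquine. Under the national-policy statement, any child treated for malaria before the December sample would lose that property. If SP and amodiaquine select for these markers, as the trial presumes, the affected contrasts would shrink.

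A smaller question sits in section 5. It does not say whether the child febrile at a round is treated whatever the test shows, or only if the test is positive. Section 7 removes a child from risk for 28 days only after a confirmed attack, so a slide-negative child treated at a round would go on being counted as at risk.

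**Working it through.** **Step 1: can the statements be followed together?**

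| Section | Who | Treatment |
|---|---|---|
| 5 | children febrile at a dosing round | Coartem after testing |
| 7 | slide-positive symptomatic cases | Coartem, then quinine if parasites persist |
| 15 | all malaria cases, in health centres | national policy |
| 1.3 | official first line | SP plus amodiaquine |

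The setting does not separate them. The outline (Follow-up) and section 7 place treatment of study cases in the same health centres that section 15 refers to. Sections 7 and 15 therefore cover the same children and agree only if Coartem is national policy, which the protocol never says. Equating the official instructions of section 1.3 with the national policy of section 15 is an inference, but it is the only content the text gives that policy.

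**Step 2: which contrasts would be touched under the national-policy statement?**

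- dhfr/dhps: the control is artesunate-amodiaquine. Its treated children would receive SP. Affected.
- pfcrt: the controls are the SP arms and Lapdap. Their treated children would receive amodiaquine. Affected.
- AS1+SP versus AS3+SP (one or three days of artesunate with SP): both arms already receive SP at all three rounds. Little affected.

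**Step 3: how many children would be treated?** Section 4 (Sample size calculations) expects 20% cumulative incidence on AS3+SP, aims to show no more than 30% in the other arms, and counts 336 evaluable children of 420 randomised per arm.

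- At 20%: 336 × 0.20 = 67.2, the plan's own 67.
- At 30%: 336 × 0.30 = 100.8, about 101.
- Of all 420 randomised: 420 × 0.20 = 84, and 420 × 0.30 = 126.

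These are whole-study counts. The last round is in early November and the survey is one month later. Follow-up runs through December (section 7), or for five months from 1 September (section 17). Some episodes would come after the sample and could not affect it.

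**Step 4: what might dilution do?** Section 4 states 77% power for 90% versus 70% with 67 per arm, two-sided 5%. With the continuity-corrected formula,

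power = Φ{ [ |p1 − p2| − 1/n − 1.96 √(2p̄(1 − p̄)/n) ] / √[ (p1(1 − p1) + p2(1 − p2))/n ] },

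and n = 67, p1 = 0.90, p2 = 0.70, p̄ = 0.80:

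(0.2000 − 0.0149 − 0.1355) / 0.0669 = 0.742, and Φ(0.742) = 77.1%. The stated figure reproduces.

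Now suppose a share f of the isolates in the 70% group moves to 90%, so that p2 = 0.70 + 0.20f. This is an assumption; the documents give no value of f.

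| f | p2 | Power |
|---|---|---|
| 0 | 0.70 | 77% |
| 10% | 0.72 | 69% |
| 20% | 0.74 | 59% |
| 30% | 0.76 | 49% |

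The table shows sensitivity only. f is a share of genotyped isolates, whereas Step 3 gives a share of children. Section 8 genotypes children who are parasite-positive at the surveys, and the proportion of those who had been treated before December may be higher or lower than 20% to 30%. The protocol states no power for the pfcrt contrast, so no similar calculation is offered for it.

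**The case against.** The best defence is that sections 5 and 7 are the operative text, agree on the drug, and set out a study-specific pathway. Section 15 is one sentence of ethical reassurance about access to care and names no drug; section 1.3 is background. On this view the centres would simply follow section 7. That may well be the intention, and it makes the dilution conditional. It does not remove the conflict: section 15 covers all cases, and nothing states that section 7 prevails.

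Several stronger readings are tempting, and the documents do not support them.

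- A reader might infer that sections 5 and 7 contradict each other on who is treated. The testing step in section 5 makes a conditional reading natural, and section 7 does not confine Coartem to slide-positive cases only. This is an ambiguity.
- A reader might infer that whole control groups would be exposed. Only children treated for malaria would be.
- A reader might take one in five as the upper limit of exposure before the December survey. The 20% is the whole-study expectation for AS3+SP. The other arms are planned against a 30% limit, and not every episode precedes the survey.
- A reader might infer that all arm comparisons are pulled towards no difference. AS1+SP versus AS3+SP is the plain exception.
- A reader might propose dropping rescued children from the resistance analysis. Rescue is a post-randomisation event and is essentially the efficacy outcome. Section 4 also counts the resistance endpoint among cases, so if rescue contained SP or amodiaquine the exclusion could remove the very 67 per arm on which the 77% rests.

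**Conclusion.** The inconsistency is real and should be corrected: Coartem in sections 5 and 7, national policy in section 15, and SP plus amodiaquine as the only official first line named, with chloroquine still in wide use (section 1.3). This rests on reading the official instructions as the national policy.

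The consequence for the resistance endpoint is conditional on section 15 being followed as section 1.3 describes the policy. In that case the artesunate-amodiaquine control for dhfr/dhps and the SP and Lapdap controls for pfcrt would be partly exposed to the drugs they control for, and those contrasts could be diluted. Roughly 20% to 30% of children per arm would be treated over the whole study. The share among genotyped isolates is unknown, so the bias in marker prevalence cannot be sized from the protocol. No figure stated in the protocol is wrong because of this point.

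**What to change.** 1. Reconcile sections 1.3, 5, 7 and 15 into one rescue rule that applies at all three health centres. Which drug it names is a clinical decision for the investigators and is not proposed here.
2. State in section 5 whether treatment at a dosing round depends on the test result.
3. Record the drug and date of every non-allocated antimalarial at all three centres. Appendix 4 has a treatment column, but the form is a passive-surveillance sheet headed for one centre. The monthly outputs in section 13.3 mention only chloroquine metabolites in urine.
4. Keep every randomised child with a genotyped sample in the main resistance analysis. Use rescue exposure before the December sample only in a secondary sensitivity analysis, labelled as conditioning on a post-randomisation event.

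The cost is a few sentences of protocol text, a drug and date entry on forms used at all three centres, and one secondary analysis. No extra children, visits or samples are needed.
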